### Interventions for malnutrition during pregnancy

#### Ready-to-use supplementary food

Linear programming (LP) technology, a formulaic computer database program listing all potential ingredients, nutritional composition, prices, and country specific availability for Sierra Leone has been used to develop and optimize the RUSF. The RUSF will be produced by Project Peanut Butter (PPB), Sierra Leone, a local non-profit organization that produces and distributes ready to use therapeutic foods. PPB operates a factory in Freetown, Sierra Leone that has been internationally certified to supply RUSF to UN agencies.

The spreadsheet-based tool identified a low-cost formula for RUSF for pregnant women. The tool allows users to consider essentially any candidate ingredient, as long as data on nutrient content, technical parameters, and prices are available. A preliminary step in the RUSF development process was conducting a price survey of all potential local ingredients that could be used in a formulation. An initial list of 89 possible locally-available candidate ingredients was identified through the following multi-step, systematic approach:National statistics on production and importation of cereals/grains, legumes, nuts, seeds, milk products, sweeteners, and oils were compiled from the Food and Agriculture Organization (FAO) and African Development Bank (ADB). All ingredients that had reported production and/or import volumes above the defined locally-available cutoff were added to the list.It was assumed that the agricultural commodity markets would be similar between Ghana and Sierra Leone since both countries are located in West Africa; therefore, locally-available candidate ingredients from a previous model used in Ghana not represented in FAO and ADB statistics were added to the list.Any additional candidate ingredient requests from the food technologists not previously included were added to the list.A few additional commodities were identified as possible candidate ingredients based on a wholesale market assessment after visiting two large markets in Freetown.

After this draft list was developed, additional ingredients were excluded based on feedback from local producers, nutritionists, food technologists, Sierra Leone government ministries, and other local experts. A subsequent list of 27 locally available candidate ingredients remained following these additional exclusions. The final candidate ingredient list for the Sierra Leone model consisted of 53 ingredients (Table 1).

**Table 1 Tab1:** Candidate ingredient list of locally produced and imported foods

Ingredient	Source Designation
Cereal/Grain, Bulgur	Locally-Available
Cereal/Grain, Cous	Locally-Available
Cereal/Grain, maize, dried, raw	Locally-Available
Cereal/Grain, Maize, yellow, flour of whole-grain	Locally-Available
Cereal/Grain, millet, Pearl, whole grain, raw	Locally-Available
Cereal/Grain, rice flour, white	Locally-Available
Cereal/Grain, rice, brown	Locally-Available
Cereal/Grain, Rice, Local Mende	Locally-Available
Cereal/Grain, Rice, White	Locally-Available
Cereal/Grain, Sorghum	Locally-Available
Cereal/Grain, wheat flour, whole grain	Locally-Available
Copalis Nutripeptin	Imported
Imperial-Oel-Import Handelsgesellschaft mbH Maris Powder ED 0106	Imported
InnoBio Algae Oil Powder	Imported
InnoBio InnoMega Alpha Linolenic Acid 80% EE	Imported
Kelatron Corporation CALCIUM RICE CHELATE 30%	Imported
Legume, Beans, Broad beans (Vicia faba)	Locally-Available
Legume, beans, chickpea flour	Imported
Legume, Beans, Cowpea, (Vigna spp.)	Locally-Available
Legume, Beans, Dry, Other, […] (Phaseolus vulgaris)	Locally-Available
Legume, Beans, Pigeon pea, […] (Cajanus cajan; C. indicus)	Locally-Available
Legume, Groundnut flour, defatted	Imported
Legume, Groundnut paste	Imported
Legume, groundnut, Bambara groundnut, dried, raw	Locally-Available
Legume, groundnut, high oleic, roasted	Imported
Legume, groundnut, shelled, local PPB source	Locally-Available
Legume, Soy flour, defatted	Imported
Legume, Soy protein concentrate, crude protein basis (N × 6.25), produced by acid wash	Imported
Legume, Soy protein isolate	Imported
Microalgae/whole cell algae/chlorella/blue green algae	Imported
Milk, acid casein	Imported
Milk, acid whey powder	Imported
Milk, caseinate, calcium	Imported
Milk, dry, nonfat, regular, without added vitamin A and vitamin D	Imported
Milk, dry, whole, without added vitamin D	Imported
Milk, Fatfilled, dry	Imported
Milk, Milk protein concentrate	Imported
Milk, Reduced lactose whey	Imported
Milk, rennet casein	Imported
Milk, sweet whey powder	Imported
Milk, whey protein concentrate 34	Imported
Milk, whey protein concentrate 80	Imported
Milk, whey protein isolate	Imported
NuMega Fish Oil Powder	Imported
Oil, Canola, Rapeseed	Imported
Oil, Fish oil, menhaden	Imported
Oil, Groundnut	Locally-Available
Oil, Linseed	Imported
Oil, Maize	Imported
Oil, Palm	Locally-Available
Oil, Palm kernel	Locally-Available
Oil, Soybean	Locally-Available
Oil, soybean, high oleic, Plenish	Imported
Seed, Melon	Locally-Available
Seed, sesame flour, partially defatted	Imported
Seed, Sesame seed (Sesamum indicum)	Locally-Available
Spirulina	Imported
Sugar, brown	Locally-Available
Sugar, white	Locally-Available
Tuber/Root, Cassava flour	Locally-Available
Tuber/Root, Cassava, gari	Locally-Available

Using the LP tool designed for Sierra Leone, preliminary formulations were generated in the Food and Nutrition Food Lab at Washington University School of Medicine (WUSTL). Four potential RUSF formulas were created at WUSTL that contained peanuts, milk powder, vegetable oil, sugar, and a vitamin mineral complex. The major difference between the four was the indigenous ingredient present: millet, split pea, cowpea, bambara bean. These four potential RUSF formulas were then tested informally by pregnant women at an antenatal clinic in Pujehun, Sierra Leone. Informal acceptability showed the formula with millet was the overwhelming favorite. The millet formula was further optimized for nutrient content, feasibility of production and organoleptic acceptability. Rudimentary blending and heating techniques were used to create a homogenous lipid matrix containing a variety of legumes, cereals, milk powders, vegetable oils, sugar, vitamin mineral complex and an emulsifying agent until the final formula was determined.

Table 2 specifies the ingredient composition of the study RUSF, named *Mama Dutasi*. The RUSF will provide a total of 520 kcal, 18 g protein, 200% of RDA for most micronutrients during pregnancy (Table 3). The supplement has also been optimized to provide excellent protein quality. The formulation contains an optimal polyunsaturated fatty acid composition by reducing the percent of energy from linoleic acid (omega-6) and increasing the percent of energy from α-linolenic acid (omega-3) to 4.5% and 1.5%, respectively [36–38].

**Table 2 Tab2:** RUSF Ingredient Composition

Ingredient	Amount (g)
Cereal/Grain: Whole, raw pearl millet	7.500062
Milk: Dry, nonfat without added vitamin A and vitamin D	21.49301
Milk: Whey protein isolate	6.832923
Palm oil	2.160523
High oleic soybean oil	25.64348
Brown sugar	20
Legume: Shelled groundnut	10

**Table 3 Tab3:** Nutrient profile of study foods

Nutrient (units)	RUSF	CSB+ with sugar, oil. Iron/folic acid^b^	RDA for pregnancy, 19–30 yr	UL (Tolerable Upper Limit Intake)
Energy, Kcal	520	1177		
Protein, g	18	35		
N-6 (% from energy)	4.5	7.3^c^		
N-3 (% from energy)	1.5	.7^c^		
Vit A (mcg)	770	2621	770	3000
Vit B1/Thiamine (mg)	2.8	0.5	1.4	
Vit B2/Riboflavin (mg)	2.8	3.5	1.4	
Vit B3/Niacin (mg)	32	20	18	35
Vit B6 (mg)	3.8	2.5	1.9	100
Vit B12 (mcg)	5.2	5.0	2.6	
Folic acid (mcg)^a^	500	275	400	1000
Vit C (mg)	170	225	85	2000
Vit D (IU)	1200	1104	600	4000
Vit E (mg)	30	20.8	15	1000
Iron (mg)	30	66.5	27	45
Zinc (mg)	22	12.5	11	40
Calcium (mg)	1600	905	1000	2500
Chromium (mcg)	60		30	
Copper (mcg)	2000		1000	10,000
Iodine (mcg)	300	100	220	1100
Magnesium (mg)	300		350	350
Selenium (mcg)	120		60	400

^a^ Amount recommended for supplementation, with 200 mcg to come from dietary sources for total RDA of 600 mg/d

^b^ Daily ration: 250 g supercereal (CSB+) with sugar, 20 ml oil, 60 mg Fe supplement with 400 mcg folic acid

^c^ Calculated based on a WFP supercereal product containing ~ 64% corn, ~ 24% soybean,~ 20 ml vegetable oil

Large scale production of this product requires the millet be in pre-processed form. The most effective pre-processing methods are roasting or extrusion cooking followed by milling. In this instance, the process used was sorting, drying, roasting, and milling. Pre-processing was performed at FINIC Industries in Kissy, Sierra Leone. The following outlines the pre-processing of millet in more detail:

##### Sorting

Proper sorting and cleaning is a necessary step to all raw commodities regardless of the harvest process. Sorting/cleaning the millet required removing dirt, debris, and stones. Visible debris like twigs and grass were removed by hand while dirt and stones were removed with a de-stoner. Once cleaned, the millet was allowed to drain.

##### Roasting and drying

Roasting is a dry heat method which bakes/toasts the ingredients. The whole grains will be placed in a rotary oven heated by charcoal and dried for 12+ hours. This process is used to destroy microorganisms, lower the water activity, inactivate enzymes and catalyzes flavors via browning reactions.

##### Milling

Milling or size reduction of whole grains was necessary prior at incorporating into the process line as to not damage the existing equipment. Size reduction of ingredients is also important for edibility. Although grinding of the final product occurs during the production process for particle reduction and homogenization, it is important that the millet have a small enough particle size to not damage the grinder plates.

The roasted, cooled, dried millet was ground to a particle size similar to baking flour and packaged in clean lined peanut buckets. The millet flour was cleared by quality control and food safety testing for microbial contamination at Eurofins Scientific Inc., Des Moines, Iowa, USA and was stored until production of the RUSF product.

The final product was packaged in 100 g foil sachets and identified with a custom *Mama Dutasi* label. Analytical testing was performed for food safety and quality assurance for aflatoxin and microbial contamination at Eurofins Scientific Inc., Des Moines, Iowa, USA.

#### Control group food

The control group will receive the standard of care for malnourished pregnant women in Sierra Leone which is 3.5 kg super cereal with 350 mL vegetable oil every two weeks. This provides 250 mg portion per day of the super cereal and 25 g oil per day for the mother. Iron and folic acid supplement goal is 90 pills through pregnancy.

The study will assure that women have an uninterrupted access to the ready to use local supplementary food and super cereal if they are in the control group. Table 3 provides a comparison of the nutritional composition of the study RUSF, standard of care food, and recommended daily intake for pregnancy. Women will receive the food for the duration of their pregnancy.

### Interventions to reduce inflammation

The intervention group will receive a package of five interventions aimed at decreasing the burden of infections in pregnant women in order to decrease the risk of stillbirth, fetal growth restriction, and premature delivery. This package will include an insecticide-treated mosquito net at the time of enrollment, sufadoxine-pyrimethamine given every 4 weeks beginning at 13 weeks gestation, azithromycin given at the time of enrollment and at 28–34 weeks of gestation, single dose of albendazole at enrollment, and testing and treatment for bacterial vaginosis at enrollment and again in the third trimester. Table 4 details the anti-inflammatory interventions.

**Table 4 Tab4:** Anti-Inflammatory Interventions, Dosing, and Timing of Administration

Intervention	Dose	Time of administration
Insecticide-treated mosquito net	n/a	• Enrollment
Sulfadoxine-pyrimethamine	1500 mg/ 75 mg	• Enrollment or 13 weeks gestation, whichever is later • Every 4 weeks until delivery
Azithromycin	1 g	• Enrollment or second trimester, whichever is later • Weeks 28–34
Albendazole	400 mg once	• Enrollment or second trimester, whichever is later
Testing and treatment for bacterial vaginosis with metronidazole	750 mg PO daily for 7 days	• Enrollment • Weeks 28–34

The control group will receive the current recommendations of the government of Sierra Leone, which includes 60 mg iron and 400 μg folic acid supplementation starting at enrollment, an insecticide-treated mosquito net at the time of enrollment, three doses of sulfadoxine-pyrimethamine during second and third trimester, and a single dose of albendazole for deworming at enrollment.

Table 5 provides a summary of the schedule of activities and interventions for subjects by week of study participation.

**Table 5 Tab5:** Schedule of activities/ interventions for subjects by week of study participation

	Study Period									
	Enrollment									
Week	0	2	4	6	8	Third trimester	Delivery	6 weeks post-partum	3 months post-partum	6 months post-partum
Enrollment:										
Eligibility Screen	X									
Informed consent	X									
Socio-demographic questions	X									
Assessments:	X				X					
HFIAS^a^, Food frequency questionnaire	X				X					
Clinic visit for intervention and control food supply	X	X	X	X	X					
Adherence/educational messages	X	X	X	X	X					
Surveillance of clinical events	X	X	X	X	X					
Maternal anthropometric measurements	X	X	X	X	X					
Infant anthropometric measurements							X	X	X	X
Interventions:										
Food distribution	X	X	X	X	X	X				
Bed net distribution	X									
Testing and treatment of bacterial vaginosis	X					X				
Albendazole (400 mg)	X									
Azithromycin (1 g)	X					X				
Sulfadoxine/ pyrimethamine (1500 mg/75 mg)	X		X		X	X				

^a^*HFIAS* household food insecurity assessment scale

Food Safety specifications: RUSF specifications will be in accordance with the CODEX guidelines for supplementary food products [39].

### Data management and analysis

Clinical data including demographics, anthropometry, morbidity, and mortality data will be collected by field workers using standardized forms. Field workers will be trained in the questionnaires and measurements prior to collecting any data. Completed data forms will be stored in a secure locked central location. All data will be double entered, compared, and sealed in a password-protected electronic database before the randomization code is broken. All data discrepancies will be resolved by examination of the original data cards and discussion with the relevant field workers. The data set will be locked after all discrepancies have been resolved.

### Statistical analysis

Descriptive statistics will be used to characterize the population. Student’s t-test will be used to assess whether primary outcomes of infant birth weight and length, and secondary outcome of maternal weight gain improved significantly in the intervention group compared with the control. Fisher’s exact test will be used to determine if the proportion of mothers recovering from malnutrition and of infants with LBW are improved in the intervention group. Regression modeling will be used to investigate factors that influence maternal and infant outcomes. Independent variables to be considered as covariates for inclusion in the models include: maternal age, weight, number of previous pregnancies, anemia, illness and number of weeks of intervention. For longitudinal measures, the groups will be compared using repeated measures mixed model analysis of variance. Covariates will include age, number of previous pregnancies, years of education and clinic location.

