### Study location

The study will enroll patients at twenty antenatal clinics in rural Pujehun District in southern Sierra Leone and 10 antenatal clinics in the Rural Western Area District. In 2013, Pujehun District had the highest rate of under 5 stunting at 46.4% which is 8.4% above the national rate. Mothers who are thin (BMI < 18 kg/m^2^) are more likely to have children that are stunted, identifying Pujehun as an ideal district for a maternal nutrition intervention. The population predominantly belongs to the Mende ethnic group. Plantation farming is a major economic activity in the region with agricultural production of palm oil, cassava, and sweet potatoes [34]. Pujehun is one of the country’s poorest and least developed districts.

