### Outcome measures

The primary outcome measure of interest will be birth length in centimeters. The secondary outcome measures of interests include the total and average weekly maternal weight gain, recovery from maternal malnutrition identified as a MUAC > 23, newborn head circumference, birth weight, infant linear and ponderal growth, and infant survival at 3 months and 6 months.

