### Sample size

The sample size will be 1514 pregnant women with malnutrition, divided equally between RUSF and control groups. This sample size allows for a 20% drop out rate and/or exclusion rate due to fundal height, leaving a final sample size of 1200 (600 per group) with a two tailed significance of 0.05, power of 80%. This will allow for detection of a difference of 0.22 SD or 0.5 cm in birth length and a difference of 0.19 SD or 80 g in birth weight.

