### Subject participation and data collection

A study team member will attend each participating antenatal clinic for subject recruitment. All women attending the antenatal clinic will be briefly informed of the study and entry criteria in a group setting. Women willing to be measured and potentially participate will be offered measurement of MUAC and screened for study eligibility.

All women meeting eligibility criteria will be offered enrollment and agree via informed consent. Informed consent will be obtained by the on-site study coordinator. All participants who are 16 years of age or older will be able to consent for themselves as adults. If a participant who is younger than 16 wants to participate in the study, they will be required to have consent from a parent or guardian. Upon enrollment, the participant will be interviewed. Demographic information will be recorded, as well as, time of last menses, estimated date of delivery, and fundal height. Anthropometry will include current weight, height, MUAC, and weight history if available. Available medical records of the women will be reviewed with attention to any current or previous pregnancy complications and medications. Subjects will answer a standard clinical symptoms questionnaire, a food frequency questionnaire, and a Household Food Insecurity Access Scale (HFIAS).

Participants will return for follow-up every 2 weeks for measurements and provision of food until delivery. Since birth measurements are primary outcomes, a birth weight team will be identified and trained in order to obtain accurate birth measurements within 48 h of delivery.

Participation in the study will continue throughout pregnancy, and follow-up with the mother and infant will continue until 6 months postpartum. Mothers and infants will be followed at usual infant clinic follow-up at 6 weeks, 3 months, and 6 months post-partum contact point clinic. Infant weight, linear growth, and morbidity will be monitored. Maternal weight, MUAC and morbidity will be assessed at these visits, as well.

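### The primary comparison of birth length is an unadjusted t-test; a short prespecified baseline adjustment would be a free, modest gain in precision

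*Protocol article*

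**What the plan says.** All places are in the Methods/design part of the protocol article.

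- **Outcome measures:** "The primary outcome measure of interest will be birth length in centimeters".
- **Statistical analysis, primary comparison:** a Student's "t-test will be used to assess whether primary outcomes of infant birth weight and length", and also the secondary outcome of maternal weight gain, improve in the intervention group. No covariate is attached to this test.
- **Statistical analysis, regression:** models are planned to explore what drives maternal and infant outcomes. The candidates are maternal age, weight, number of previous pregnancies, anaemia, illness and length of time on the intervention.
- **Statistical analysis, longitudinal measures:** a repeated-measures mixed model is named, and the next sentence reads "Covariates will include age, number of previous pregnancies, years of education and clinic location". Clinic appears nowhere else in the analysis text.
- **Subject participation and data collection:** at enrolment, demographics, last menses, expected delivery date and fundal height are recorded. "Anthropometry will include current weight, height, MUAC, and weight history if available".
- **Study location:** women come from "twenty antenatal clinics in rural Pujehun District in southern Sierra Leone and 10 antenatal clinics in the Rural Western Area District".
- **Randomization and blinding:** women are allocated individually by a random number generator. No stratification by clinic is stated.
- **Sample size:** 600 evaluable women per group, "with a two tailed significance of 0.05, power of 80"%, for "a difference of 0.22 SD or 0.5 cm in birth length" and "a difference of 0.19 SD or 80 g in birth weight".

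**The concern.** The primary estimate uses nothing measured before randomisation. Whatever part of the variation in birth length comes from stage of pregnancy at entry, maternal size, parity, age, clinic or district stays in the error term of the t-test.

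The plan does not treat covariates consistently. Read in sequence, repeated measures are adjusted for clinic, while length at birth is compared without adjustment, and no reason is given. The Study location section itself links maternal thinness to child stunting and describes Pujehun's stunting rate as above the national one, while a third of the clinics lie in another district. Variation by maternal size and place is therefore plausible on the article's own account.

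The planned regression cannot serve as the adjusted treatment comparison. Its purpose is exploratory and its covariates are only candidates. It also lists time on the intervention, which depends on when the woman delivers, and the package aims to change that. Conditioning on it would distort the treatment effect.

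At stake is the width of the interval around the primary estimate, not the validity of the test.

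**Working it through.** **Inputs.** From Sample size: 600 per group, two-sided 0.05, 80% power, 0.22 SD = 0.5 cm. Implied SD = 0.5/0.22 = 2.27 cm. The article gives no R-squared or intraclass correlation for birth length, so R² = 5%, 10% and 20% are assumptions that show a range.

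**1. The plan's own figure.** n per group = 2(1.96 + 0.84)²/0.22² ≈ 325. The stated 600 per group does not follow from 0.22 SD at 80% power. With 600 per group:

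- SE = 2.27 × √(2/600) = 0.131 cm
- 95% half-width = 1.96 × 0.131 = 0.26 cm
- power for 0.5 cm = Φ(0.5/0.1312 − 1.96) = 96.8%
- power for the birth-weight effect of 0.19 SD = 90.8%
- difference detectable with 80% power = 0.162 SD, or 0.37 cm

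The mismatch in the sample-size statement is a separate matter. Here it matters only because the trial starts with more power than it states.

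**2. Gain before the cost of covariates.** SE ratio = √(1 − R²); equivalent N = 1200/(1 − R²).

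**3. Cost of covariates.** Thirty clinics give 29 terms; with five maternal covariates that makes 34. Under unstratified allocation, chance correlation between arm and covariates multiplies the variance by about 1/(1 − 34/1199) = 1.029. A simulation with 1200 women, 30 equally likely clinics and 1:1 allocation gives the same 2.9%. Net SE ratio = √[(1 − R²) × 1.029].

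| Assumed R² | SE reduction, before cost | Extra infants equivalent, before cost | SE reduction, net | Extra infants equivalent, net | Half-width, net (cm) | Power for 0.5 cm, net |
|---|---|---|---|---|---|---|
| 0 (t-test) | – | – | – | – | 0.26 | 96.8% |
| 5% | 2.5% | 63 | 1.1% | about 27 | 0.25 | 97.1% |
| 10% | 5.1% | 133 | 3.8% | about 95 | 0.25 | 97.7% |
| 20% | 10.6% | 300 | 9.3% | about 257 | 0.23 | 98.7% |

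With all 34 terms the break-even R² is 34/1199 = 2.8%; below that, adjustment loses a little. With district in place of clinic there are six terms and the variance cost is 1/(1 − 6/1199) = 1.005, so almost nothing is lost, but variation between clinics within a district is then left in the error.

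**4. If the true effect is smaller.** For an assumed 0.3 cm, unadjusted power = Φ(0.3/0.1312 − 1.96) = 63%. Net of 34 terms it is 64%, 66% and 71% at R² of 5%, 10% and 20%.

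**The case against.** The strongest reply is that this is a preference. Under individual randomisation the t-test is valid and unbiased for the difference in mean birth length, and its standard error already allows for chance imbalance. That stands, and nothing here calls the test wrong. It is also true that covariate details are often left to an analysis plan. But the article does more than stay silent: it names the unadjusted test for the primary outcome.

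Several stronger readings are tempting and are not supported:

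- **That the predictors are strong.** No figure supports this. MUAC is restricted to 23 cm or less at entry, which tends to weaken it as a predictor, and fundal height reflects gestation at enrolment, not at birth.
- **That the plan makes no use of covariates for birth outcomes.** Age, weight and parity are candidates in the planned regression for infant outcomes. The gap is that this regression is not the treatment comparison.
- **That allocation is unbalanced by clinic.** The article only states no stratification, and a condensed article's silence does not show imbalance.
- **That the trial's power is at risk.** At the stated effect it is about 97% without adjustment.

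The cost of 34 covariate terms also stands: at R² of 5% it removes more than half the gain. It argues for a short covariate list, not against adjustment.

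**Conclusion.** The point holds as a free improvement with a modest gain. The plan gives up available precision on its primary estimate by naming an unadjusted test and leaving regression to an exploratory role.

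For an assumed R² of 5% to 20%, the net reduction in standard error is about 1% to 9% with clinic terms, and the interval half-width falls from about 0.26 cm to about 0.23 to 0.25 cm. Power for 0.5 cm hardly moves. The benefit matters more if the effect is smaller, which the article gives grounds to consider: its Background reports no significant effect of earlier maternal supplementation on birth length, and its Discussion expects that controls may do better than current data suggest.

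The size rests on the assumed R², the SD implied by the Sample size section, 1200 measured infants and unstratified allocation. A reader might infer that the t-test result would be biased or wrong; the documents do not support that.

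**What to change.** Amend the Statistical analysis section before the randomisation code is broken:

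- Make the primary analysis a linear model of birth length on arm with a short prespecified set of baseline covariates: fundal height at enrolment, maternal height, MUAC or weight, parity and age, plus clinic or district. Weight history is recorded only if available and should not be in the set.
- Leave out time on the intervention and any illness arising after enrolment.
- Report the adjusted difference in centimetres with its 95% confidence interval.
- Use the same approach for birth weight and for maternal weight gain, with enrolment weight among the covariates for the latter.
- Keep the t-test as a sensitivity analysis, and label the existing regressions as exploratory.

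The choice between clinic and district should be fixed in advance: clinic captures more variation, and district costs fewer terms. The change is to wording only. It needs no new data, visits or participants.

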**Methods/design:**

This will be a prospective, randomized, controlled clinical effectiveness trial of an improved supplementary food plus anti-infective therapies compared to standard therapy in malnourished pregnant women. Pregnant women will be randomized to receive a low water activity, ready-to-use supplementary food plus five anti-infective interventions or the standard of care which is 3.5 kg corn/ soy blended flour with 350 mL vegetable oil every two weeks. The five anti-infective interventions are 1) insecticide-treated mosquito net at the time of enrollment into the study, 2) sulfadoxine-pyrimethamine given every 4 weeks, beginning at enrollment or at 13 weeks’ gestation, whichever is later, 3)azithromycin at a dose of 1 g given once at enrollment (after first trimester)and again during 28–34 weeks of gestation, 4)single dose 400 mg albendazole given in second trimester, and 5) testing and treatment for bacterial vaginosis at enrollment and again at 28–34 weeks of gestation. Treatment will be provided for the duration of the pregnancy. The primary outcome measure will be birth length. Secondary outcomes in the mothers will include rates of maternal weight gain and increase in mid-upper arm circumference, and time to maternal anthropometric recovery. Secondary outcomes in the infants will include birth weight, birth head circumference, and linear and ponderal growth.

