One limitation of the study is the lack of blinding of the nutritional and anti-infective interventions between the two groups. The study RUSF and standard of care flour are distinctly different in packaging and appearance. Those participants randomized to the intervention group will receive more obvious anti-infective interventions during antenatal visits. Mitigating the un-blinded nature of the intervention distribution is that choice of primary outcome, birth length, will be obtained in a standardized, objective manner. In order to account for this lack of blinding, study managers will be blinded to treatment during data analysis. Another limitation is the possibility that participants will share or trade their assigned food. Participants will be educated about the need to comply with the assigned intervention. We anticipate this will be an unlikely occurrence as past research by our group of compliance with supplementary foods in Malawi rarely demonstrated sharing or trading of assigned foods [44]. An additional limitation of our data will be that the control group will be receiving the standard of care for Sierra Leone, but these interventions are not universally adopted, especially in very rural areas such as Pujehun. This may result in improved outcomes in the control group than would be expected from currently available data for pregnant women and infants.

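### The statistical analysis section ranks birth weight as a primary outcome beside birth length, while the abstract, outcome section and discussion name birth length alone

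*Protocol article*

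**What the plan says.** Three places give a single primary outcome:

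- Abstract, Methods/design: "The primary outcome measure will be birth length". Birth weight is then placed in the lower tier: "Secondary outcomes in the infants will include birth weight, birth head circumference, and linear and ponderal growth".
- Outcome measures: "The primary outcome measure of interest will be birth length in centimeters". Its list of secondary outcomes includes "newborn head circumference, birth weight, infant linear and ponderal growth, and infant survival at 3 months and 6 months".
- Discussion, limitations paragraph: in defending the unblinded design it relies on the "choice of primary outcome, birth length, will be obtained in a standardized, objective manner", in the singular.

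Two places use the plural:

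- Statistical analysis: Student's t-test is to assess "primary outcomes of infant birth weight and length, and secondary outcome of maternal weight gain improved significantly in the intervention group".
- Subject participation and data collection: "Since birth measurements are primary outcomes", given as the reason for training a measurement team.

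The Sample size section states one two-tailed significance level, 0.05, and 80% power. It gives detectable differences for both endpoints: 0.22 SD (0.5 cm) for length and 0.19 SD (80 g) for weight. It does not say which endpoint is primary.

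**The concern.** The sentence in Statistical analysis is hard to read as loose wording. It sorts outcomes by rank within one clause, with maternal weight gain in the secondary tier and birth weight in the primary tier. That conflicts directly with the Outcome measures section.

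The interpretation of the trial is at stake. Suppose birth weight differs significantly and birth length does not. A reader of Statistical analysis could report success on a primary outcome, while a reader of the abstract, Outcome measures or the Discussion would report that the primary outcome was not met. A reading that lets either endpoint carry the claim would also raise the chance of a false claim above the nominal level. The Discussion offers the intervention as a possible model for national programmes, so this should be settled before the randomization code is broken.

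**Working it through.** **1. Rank of birth weight, section by section**

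| Section | Birth length | Birth weight |
|---|---|---|
| Abstract, Methods/design | primary | secondary |
| Outcome measures | primary | secondary |
| Discussion | primary (singular) | not ranked |
| Statistical analysis | primary | primary |
| Subject participation and data collection | birth measurements called primary | same |
| Sample size | detectable difference given | detectable difference given |

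The contradiction is complete at this step and needs no arithmetic.

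**2. The plan's own sample size**

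Inputs from the Sample size section: two-sided alpha 0.05, power 80%, effects 0.22 SD and 0.19 SD, 600 per group.

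n per group = 2(1.960 + 0.842)² / d²

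- Length, d = 0.22: 325 per group.
- Weight, d = 0.19: 435 per group.

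The stated 600 is therefore not reproduced at 80% power. Using power = Φ(d√(n/2) − 1.960) with n = 600:

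- Length: Φ(3.811 − 1.960) = 97%.
- Weight: Φ(3.291 − 1.960) = 91%.

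The mismatch is a separate matter. It bears on this point only in that the sample has room for either repair below.

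**3. Error rate if either endpoint were enough**

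Assumptions, neither of which is in the document: success on either endpoint counts, and the two test statistics are bivariate normal with correlation ρ.

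- Two-sided familywise error = 1 − P(|Z₁| < 1.96 and |Z₂| < 1.96). At ρ = 0 this is 1 − 0.95² = 0.0975.
- Favourable direction only = 1 − P(Z₁ < 1.96 and Z₂ < 1.96).

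| ρ (assumed) | Two-sided | Favourable only |
|---|---|---|
| 0 | 9.75% | 4.9% |
| 0.5 | 9.1% | 4.5% |
| 0.7 | 8.35% | 4.2% |
| 0.8 | 7.8% | 3.9% |
| 0.9 | 7.0% | 3.5% |
| one endpoint only | 5% | 2.5% |

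**4. Error rate if both endpoints were required**

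Two-sided: 0.05 + 0.05 − (either-endpoint error). At ρ = 0 this is 0.10 − 0.0975 = 0.25%. At ρ = 0.7 it is 0.10 − 0.0835 = 1.65%. Under that rule there is no inflation.

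**5. Two primaries at 0.025 each**

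The critical value is 2.241 and n = 600 per group.

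- Length: Φ(3.811 − 2.241) = 94%.
- Weight: Φ(3.291 − 2.241) = 85%.

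Familywise error is at most 5%.

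**The case against.** The strongest reply is that the document conflicts on labels only and defines success nowhere. The either-endpoint rule is therefore an inference. The Discussion speaks of infants being both longer and larger, which fits a both-endpoints reading at least as well, and under that reading nothing is inflated. A rule linking the two tests is also commonly left to a full protocol or SAP, so its absence here is no fault. All of this stands. It limits the error-rate argument but not the contradiction, because an SAP rule would not make the article's sections agree.

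Two supporting places are weak. The remark in Subject participation and data collection explains why a team is trained and sets no analysis hierarchy. The Sample size section covers both endpoints and leaves open that two primaries were intended.

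Two stronger readings are tempting, and the document supports neither:

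- A reader might infer an 8% to 10% chance of false primary success. That range is a two-sided error that also counts significant harm, whereas the stated question is improvement. It depends on a correlation the document does not give, and at 0.8 or 0.9 the two-sided figure is already below 8%.
- A reader might infer that a weight-only result is the likely one, because the Background reports that other supplements raised birth weight without affecting length. Those trials tested other products. Here the control arm is also fed: Table 3 gives 1177 kcal for its daily ration against 520 kcal for the RUSF. The Background also cites a Malawi trial in which azithromycin reduced stunting. A split result is possible, but nothing shows that it is likely. If the weight effect were real, a global-null error rate would not describe that case anyway.

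**Conclusion.** The point holds as a contradiction in the current text. Statistical analysis makes birth weight a primary outcome, the abstract and Outcome measures make it secondary, and the Discussion names length as the primary outcome. This is wrong as written and must be reconciled, because it decides what a weight-only result would mean.

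The size is conditional. If either endpoint at two-sided 0.05 counted as success, the two-sided familywise error would be about 7% to 10%, or 3.5% to 4.9% in the favourable direction against 2.5% for a single endpoint. This rests on a success rule the text does not state and on an assumed correlation between 0.9 and 0. If both endpoints were required, or if length alone decided, there would be no inflation.

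**What to change.** Amend Statistical analysis to name birth length as the sole primary outcome at two-sided 0.05 and birth weight as secondary. Reword the sentence in Subject participation and data collection to match. Weight could, for example, be tested confirmatorily only if length is significant, which costs length no alpha.

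If the sponsor does intend two primaries, the abstract, Outcome measures and Discussion must say so and an alpha rule must be given. A split of 0.025 each is one option, with the power shown above.

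Either route needs only changes of wording and no further participants. With length as the sole primary outcome, the price is that an effect on weight alone cannot be claimed as primary success. With two primaries, the price is a few points of power: from 97% to 94% for length and from 91% to 85% for weight.
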